### 4.2. Sample Size Calculation

Our power calculations are based on a sample size that can document the superiority of yoga compared to strengthening exercise by an amount that meets the minimal clinically important difference (MCID). Based on the MCID of 15 mm in VAS pain (a numerical scale ranging from 0 (no problem) to 100 (maximum problem)), the two-sided significance level of 0.05, 90% power, and SD of VAS pain change 22.5, we will need a total of 98 participants. Assuming a scenario of around 20% dropout, we will need 126 participants.

The above sample size will allow us to detect a non-inferiority of yoga with strengthening exercise. Non-inferiority would be declared if the mean change in knee pain (assessed using VAS) in the yoga group was not significantly worse than the mean change in the strengthening exercise group, within a pre-stated margin of non-inferiority (∆), in this case, set at 10 mm. Overall, 126 participants will give us 80% power to detect the non-inferiority of yoga compared with strengthening exercise.

### 4.3. Statistical Analyses

The comparisons of pain and other continuous outcomes will be done employing a repeated-measures mixed model incorporating terms of treatment, time, and respective baseline values as covariates. The treatment effect will be calculated by the intervention by time interaction followed by the main effects model with only group and time. We will also assess the effects of potential confounders or interaction with treatment by covariates, including age, sex, BMI, disease severity, comorbidities, health status, and use of pain medications. A two-sided *p*-value less than 0.05 will be considered to indicate the statistical significance, and the results will be shown as the between-group differences with 95% confidence intervals (95% CIs) of the differences.

We will explore the role of clustering effects in the trial by performing a sensitivity analysis examining the implications of clustering by the instructor by adding an instructor random effect to our mixed-effects model.

We will also perform an exploratory analysis to investigate whether the presence or absence of neuropathic pain, as assessed by the painDETECT questionnaire, is a potential moderator that influences response to treatment for the primary outcome at 12 weeks. To assess the moderation of the effect by painDETECT (binary moderator), an interaction term between the randomised group and the potential moderator will be included in outcome regression models.

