### 3.2. Study Participants

We will recruit 126 knee OA participants with knee pain from the southern Tasmania region of Australia. Community-based recruitment will be accomplished through collaboration with general practitioners, specialist rheumatologists, orthopaedic surgeons, physiotherapists, and advertising through radio, TV, newspaper, social media, community notice boards, hospital notice boards, community newsletters, local press, physiotherapy practices, and exercise physiologists in the region. Previous clinical trial participants who expressed interest in future studies will be contacted.

Inclusion criteria:Aged ≥40 years, both males and females;Knee pain on most days for at least six months;Average VAS knee pain intensity of ≥40 mm in the last month;Meet the American College of Rheumatology (ACR) clinical criteria for the diagnosis of knee OA;Be willing to participate in a group yoga program or group strengthening exercise program two times per week for the first 12 weeks and can attend on the days/times of the week that scheduled classes are running.

Exclusion criteria:Patients currently or in the past three months engaged in strengthening exercise or yoga programs for the treatment of any disease;Other forms of inflammatory arthritis (especially rheumatoid arthritis and gout);A significant knee injury that required treatment within the last six months;Arthroscopy or open surgery in the index knee in the last six months or planned in the next 6–8 months;Partial or total knee replacement;Injections of corticosteroids (last three months) or hyaluronic acid (last six months) in the index knee;Pregnancy or breastfeeding;Currently participating in any other drug/device/exercise clinical trial related to OA;Presence of any serious medical illness or condition that may preclude a 24-week follow up;Any condition that precludes safe participation in exercise (i.e., fails the safety for exercise clearance; see below for the procedure for this);Unable to walk without a gait aid;Inability to provide informed consent in English;Plan to start an exercise-based treatment program (e.g., GLA:D) or another new treatment for knee OA in the next six months;Planned absences (e.g., trips away) of >2 weeks maximum during the 12-week period.

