### 3.8. Primary Outcome

Change in overall average knee pain assessed by visual analogue scale (VAS) over 12 weeks.

Pain will be evaluated at each time point using a 100 mm VAS and asked: “On this line, how would you rate your overall average knee pain in the last one week?” For knee pain assessed using VAS, terminal descriptors will be 0 mm = no pain to100 mm = worst pain possible.

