## Figures and Tables

**Figure 1 jfmk-07-00084-f001:**
[figure not shown]
Trial design.

**Table 1 jfmk-07-00084-t001:** SPIRIT (Standard Protocol Items: Recommendations for Interventional Trials) diagram of enrolment, interventions, and assessments for the YOGA trial.

Items/Variables	Screening	Baseline (week 0)	Week 4	Week 8	Week 12	Week 16	Week 20	Week 24
Informed consent	x							
Randomisation		x						
Safety for exercise clearance	x							
ACR clinical criteria for knee OA	x							
Medicare number		x						
Clinical measures								
Blood (stored for cartilage/synovium/ inflammatory markers)		x			x			x
Core physical function tests		x			x			x
Leg muscle strength test		x			x			x
Height and weight		x			x			x
Gait characteristics		x			x			x
Body composition (using BIA)		x			x			x
Physical activity (using accelerometers)		x						x
Questionnaires								
Knee pain VAS	x	x	x	x	x	x	x	x
Knee WOMAC		x	x	x	x	x	x	x
PainDETECT		x			x			x
PHQ-9		x			x			x
Patient global evaluation		x	x	x	x	x	x	x
Pain medication use/change in use		x	x	x	x	x	x	x
Health Economics Outcomes: Medication cost diary Health service utilisation (visit to GP, practice nurses, and any other health professionals (e.g., physiotherapists)) Employment/days off work Concession/health care card Private health insurance Transport and specialised equipment costs		x			x			
Safety (AEs)			x	x	x	x	x	x
EQ-5D and AQoL-8D		x			x			x
Consent to contact for future studies								x
Early withdrawal information		As required						

ACR, American College of Rheumatology; AE, adverse events; AQoL-8D, Assessment of Quality of Life-8 dimension; BIA, Bio-Electrical Impedance Analysis; EQ-5D, European Quality of Life Five Dimension; GP, general practitioner; OA; osteoarthritis; PHQ-9, Patient Health Questionnaire-9; VAS, visual analogue scale; WOMAC, Western Ontario and McMaster Universities Osteoarthritis Index.

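### The primary model adjusts for the week-0 knee pain VAS only and leaves the scheduled screening VAS unused, forgoing a modest and almost free gain in precision

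*Protocol article*

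**What the plan says.** - **Outcome.** Section 3.8 defines the primary outcome: "Change in overall average knee pain assessed by visual analogue scale (VAS) over 12 weeks". It adds: "Pain will be evaluated at each time point using a 100 mm VAS and asked". The question that follows covers the last one week.
- **Schedule.** In Table 1 the knee pain VAS row is marked at screening, at baseline (week 0) and every four weeks to week 24. Randomisation is marked only in the week-0 column.
- **Model.** Section 4.3 compares groups by "employing a repeated-measures mixed model incorporating terms of treatment, time, and respective baseline values as covariates". The further covariates to be explored are listed as "including age, sex, BMI, disease severity, comorbidities, health status, and use of pain medications". The screening VAS is named in neither place.
- **Entry.** Section 3.2 requires: "Average VAS knee pain intensity of ≥40 mm in the last month".

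**The concern.** A single VAS reading is a noisy measure of a person's usual pain. A second reading before allocation usually explains some of the outcome variance that the first leaves over. Adjusting for it does not bias the treatment effect or change the type I error. If the reading is collected and left out, the interval for the primary comparison is somewhat wider than it needs to be.

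There is also a loose end about what the screening reading is. Section 3.8 ties a last-week question to each time point, Table 1 shows screening in the same undivided VAS row, and the entry criterion in Section 3.2 is a last-month average. The protocol does not say which recall period the screening VAS used. That bears on how closely the screening value resembles the week-0 value, and so on how much it can add.

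**Working it through.** **1. Reproduce the plan's figures.** Section 4.2 gives a difference of 15 mm, SD of change 22.5 mm, 90% power and "the two-sided significance level of 0.05". The normal approximation gives 48 per arm (96 in total). The t-based calculation needs 49 per arm, with power 90.4%, so the stated 98 reproduces. Inflating for 20% dropout gives 98/0.80 = 122.5, so 123; the stated 126 corresponds to 1 − 98/126 = 22%, close to the stated figure of around 20%.

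For non-inferiority at 10 mm, with a true difference of zero, the stated 80% reproduces with all 126 evaluable and one-sided alpha 0.05. The SE is 22.5 × √(2/63) = 4.01 mm, and Φ(10/4.01 − 1.645) = 80.2%. With 49 evaluable per arm it is 71.1%.

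None of these calculations takes credit for baseline adjustment.

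**2. Gain with equal correlations.** Let ρ be the correlation between any two VAS readings (assumed). For the week-12 contrast the residual variance, as a fraction of the total, is
- week 0 only: 1 − ρ²
- week 0 and screening: 1 − 2ρ²/(1 + ρ)

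| ρ | Week 0 only | Both | Variance cut |
|---|---|---|---|
| 0.3 | 0.910 | 0.862 | 5.3% |
| 0.4 | 0.840 | 0.771 | 8.2% |
| 0.5 | 0.750 | 0.667 | 11.1% |
| 0.6 | 0.640 | 0.550 | 14.1% |
| 0.7 | 0.510 | 0.424 | 17.0% |

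This is the favourable case. It ignores the entry cut-off and any fading of correlation with time.

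**3. Allow for the entry cut-off.** Suppose the screening VAS is the reading on which the 40 mm criterion is applied. Its range is then truncated and it predicts less. Simulation with an assumed mean of 45 to 55 mm, SD 22 mm and ρ of 0.4 to 0.6 before truncation gives a cut of 4% to 9%.

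A second simulation gave each person a constant usual pain level (mean 55, SD 14 to 18 mm) plus reading error (SD 10 to 16 mm at screening, 12 to 16 mm at week 0). The week-12 slope on usual pain was 0.6 to 1.0, the SD of change was held at 22.5 mm, and entry required screening VAS of at least 40 mm. The cut was 1% to 16%, with a median of 5%.

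**4. Allow for correlation that fades with time.** Let b and s be the correlations of the week-0 and screening readings with week 12, and c the correlation between the two. Then R² = (b² + s² − 2bsc)/(1 − c²).
- b = 0.5, s = 0.45, c = 0.6: R² = 0.1825/0.64 = 0.285. Residual 0.715 against 0.750, a cut of 4.7%.
- b = 0.5, s = 0.35, c = 0.7: R² = 0.1275/0.51 = 0.250. No cut.

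**5. Interval width.** With SD 22.5 mm and 49 per arm, the SE is 22.5 × √(2/49) = 4.55 mm and the half-width is 1.96 × 4.55 = 8.9 mm. A variance cut of v narrows the interval by 1 − √(1 − v):
- 5%: 2.5%, about 0.2 mm
- 8%: 4.1%, about 0.4 mm
- 15%: 7.8%, about 0.7 mm

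In sample-size terms, 5% is worth 98/0.95 = 103, or about 5 more evaluable participants.

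**6. Power.** The table takes ρ = 0.5, 49 evaluable per arm and two-sided 0.05 (normal approximation). The residual SD with week 0 only is 22.5 × √0.75 = 19.49 mm, so the SE is 3.94 mm.

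| Covariates | SE (mm) | Power, 15 mm | Power, 10 mm |
|---|---|---|---|
| Week 0 only | 3.94 | 96.8% | 71.9% |
| Both, 5% cut | 3.84 | 97.4% | 74.1% |
| Both, 11.1% cut | 3.71 | 98.1% | 76.9% |

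At one-sided 0.05, the level that reproduces the stated non-inferiority power, the 10 mm figures become Φ(10/SE − 1.645) = 81.5%, 83.2% and 85.3%.

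**The case against.** The strongest reply is that nothing here is wrong. Adjusting for the week-0 value is standard, superiority power is already above 95% at ρ = 0.5, and the gain is a fraction of a millimetre resting on correlations that the documents do not give. An extra covariate could also be added in an analysis plan that is not shown. Most of this stands, and it sets the size of the point: an inexpensive improvement to a sound model. What remains is that Section 4.3 names its covariates and omits a pre-randomisation reading that the same article schedules.

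Three stronger inferences are tempting.
- **That the primary analysis is biased or underpowered for superiority.** It is neither. Omitting a prognostic covariate in a randomised comparison costs precision only, and the sample size took no credit for baseline adjustment.
- **That the gain is large.** If the effect is averaged over weeks 4, 8 and 12, equal correlations of 0.3 to 0.7 give a cut of 11% to 28%. Those figures ignore both the entry cut-off and fading correlation, which pull the gain down.
- **That entry was judged on the wrong recall period, so a second screening question is needed.** Section 3.8 describes how the outcome is scored, and a last-month entry item can coexist with a last-week outcome item. The wording is unclear, but no error at entry is shown. A new question could not supply values for people already screened in a trial that the Abstract says is under way.

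**Conclusion.** The point holds as a modest efficiency gain. For the week-12 contrast, adding the screening VAS to the week-0 VAS cuts residual variance by roughly 0% to 15%, typically about 5%. The interval narrows by about 2.5% in the typical case and by just under 8% at the top of the range. The benefit is slight for superiority at 15 mm and somewhat greater for the 10 mm non-inferiority comparison, at about 2 percentage points of power for a 5% cut.

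This rests on assumed correlations. It also assumes that the week-0 VAS is taken before allocation (inferred from its role as baseline, since Table 1 puts both in one column) and that a screening VAS was recorded for everyone randomised. The gain may be smaller if the screening item used last-month recall, but the value would still be a legitimate covariate.

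The recall-period wording is a separate, minor point of clarity.

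**What to change.** 1. Before the data are analysed, pre-specify the screening knee pain VAS as a second continuous covariate beside the week-0 VAS, in the primary model and in the non-inferiority estimate. Use the value as already collected, whichever recall period it had, and add no new screening item. The cost is one degree of freedom and one sentence in the analysis plan. The Data Availability statement indicates that the database had not yet been analysed when the article was written.
2. Reconcile Section 3.2, Section 3.8 and Table 1 by stating which recall period the screening VAS used. A footnote to Table 1 is enough.

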### 3.9. Secondary Outcomes: The Overall Change from Baseline to Week 12 and Overall Change from Baseline to Week 24 Are Separate Outcomes

Change in VAS knee pain over 12 weeks in patients with painDETECT > 12;Change in VAS knee pain over 24 weeks;Change in Western Ontario and McMaster Universities Osteoarthritis Index (WOMAC) knee pain, WOMAC stiffness, and WOMAC knee function assessed using VAS over 12 weeks and over 24 weeks;Change in core physical function as assessed by 30 s chair stand test, 40 m fast walk test, and stair climb test over 12 and over 24 weeks.

Core physical function measures: Objective measures, including a 30-second chair stand test, 40 m (10 m × 4) fast-paced walk test, and stair climb test, will be performed as recommended by the Osteoarthritis Research Society International (OARSI) guidelines for clinical trials at baseline and week 12 using the same equipment and at the same location. The total number of chair stands in 30 s, time to complete 40 m walk with three turns, and time to ascend and descend a nine-step stair (20 cm step height and handrail) will be recorded. [37,38]

Change in biomarkers (urinary CTX-II, serum COMP, and serum hyaluronan) and systemic inflammatory markers (hs-CRP, IL-6, TNF-a) over 12 and over 24 weeks;Change in Patient Health Questionnaire (PHQ-9) scales over 12 and over 24 weeks.

Patient Health Questionnaire (PHQ-9)*:*
Depression may be an effect modifier. It will be assessed using the Patient Health Questionnaire (PHQ-9) at weeks 0, 12, and 24. The PHQ-9 is a validated tool for screening, diagnosing, monitoring, and measuring the severity of depression. It consists of nine questions based on the Diagnostic and Statistical Manual of mental disorders (DSM-IV) criteria for the diagnosis of major depressive disorders in patients with medical illnesses [39].

Change in patient global satisfaction score (assessed using a 100 mm VAS) over 12 and over 24 weeks [40]. Patients will be asked, “Considering all the ways in which illness and health conditions may affect you at this time, please indicate on the line below how you are doing ?”, along with a 0–100 VAS, where 0 is very well, and 100 is very poor;Change in neuropathic pain, as assessed by the painDETECT questionnaire, over 12 and over 24 weeks.

PainDETECT questionnaire: It uses a combination of VAS, Likert-type questions, and body diagram to ask about everyday frequency of symptoms such as “electric shocks” or “painful light touch” [41].

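### The plan's two-step treatment effect does not fix the week-12 difference in knee pain as the primary estimate, and the two quantities it names generally differ from that difference

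*Protocol article*

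**What the plan says.** Section 3.8 defines the primary outcome as "Change in overall average knee pain assessed by visual analogue scale (VAS) over 12 weeks". The heading of Section 3.9 explains this type of wording: "The Overall Change from Baseline to Week 12 and Overall Change from Baseline to Week 24 Are Separate Outcomes". The moderator paragraph of Section 4.3 also places the primary outcome at week 12.

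Section 4.2 sizes the trial for one between-group difference in change: "Based on the MCID of 15 mm in VAS pain", with "the two-sided significance level of 0.05, 90% power" and "SD of VAS pain change 22.5, we will need a total of 98 participants".

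Table 1 schedules the VAS at every time point, so there are three post-baseline readings to week 12 (weeks 4, 8, 12) and three more to week 24.

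Section 4.3 analyses pain with a repeated-measures mixed model containing treatment, time and "respective baseline values as covariates". It then states how the effect is obtained: "The treatment effect will be calculated by the intervention by time interaction followed by the main effects model with only group and time". Results are to be given as between-group differences with 95% confidence intervals. That sentence names no visit.

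**The concern.** This is a stated rule, not a detail left open, and it does not lead to the quantity the rest of the article describes. With baseline as a covariate, the outcome rows are the post-baseline visits. The group-by-time terms then describe how the treatment difference moves from one visit to another. A benefit that is the same at every visit makes them zero. The main-effects model gives one difference averaged over whatever visits are fitted.

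An analyst who follows the sentence therefore holds two results, each described as the treatment effect, with nothing to say which is primary. Neither is in general the baseline-to-week-12 difference. The primary estimate could be set beside the 15 mm MCID although it measures something else, and the choice between the two could be made after the data are seen.

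**Working it through.** **Inputs from the protocol article.** Difference 15 mm, SD of change 22.5 mm, two-sided 0.05, 90% power, total 98 before dropout (Section 4.2). 1:1 allocation (Section 3.1). VAS at weeks 4, 8 and 12 (Table 1).

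**Assumptions, not in the article.** 49 per arm analysed with complete data, SD 22.5 mm at each visit, equal between-visit correlation rho of 0.5 to 0.7, and the effect profiles below. If baseline adjustment lowers the SD, every power figure rises, but the estimates do not change.

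**1. The plan's own figure.** n per arm = 2 × (1.960 + 1.282)² × 22.5² / 15² = 2 × 10.51 × 2.25 = 47.3, so 48 by the normal approximation. The t-based calculation gives 49 per arm, 98 in total, as stated. The sizing is for one difference in mean change, not for an interaction or an average over visits.

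**2. What each model returns.** Let d4, d8 and d12 be the baseline-adjusted differences at weeks 4, 8 and 12.
- Interaction terms, week 4 as reference: d8 − d4 and d12 − d4.
- Main-effects model: (d4 + d8 + d12) / 3.
- Week-12 difference: d12. With categorical visit this is the treatment term plus the treatment-by-week-12 term.

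**3. Standard errors.**
- Week 12: 22.5 × √(2/49) = 4.55 mm.
- Visit average: 4.55 × √((1 + 2 rho)/3) = 3.71 mm at rho 0.5 and 4.07 mm at rho 0.7.
- Week 12 minus week 4: 4.55 × √(2(1 − rho)) = 4.55 mm at rho 0.5 and 3.52 mm at rho 0.7.

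**4. Results.** For a non-zero effect, power = Φ(effect/SE − 1.96). With zero effect, the two-sided test rejects at 5%.

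| Quantity | Constant 15/15/15 mm | Building 5/10/15 mm |
|---|---|---|
| Week-12 difference | 15 mm, 91% | 15 mm, 91% |
| Main-effects estimate | 15 mm, 96–98% | 10 mm, 69–77% |
| Interaction, week 12 minus week 4 | 0 mm, 5% | 10 mm, 59–81% |

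For example, week 12: 15/4.55 − 1.96 = 1.34, and Φ(1.34) = 0.91. For the main effect under build-up at rho 0.7: 10/4.07 − 1.96 = 0.50, and Φ(0.50) = 0.69.

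So the main-effects estimate equals the week-12 difference under a constant benefit, and is then more precise. Under a build-up it is 5 mm smaller. The interaction contrast does not equal the week-12 difference in either column.

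**The case against.** The strongest reply is that the week-12 difference is not lost. A mixed model with treatment, categorical visit and their interaction contains it, and Sections 3.9 and 4.3 tell the analyst which time point is meant. This stands. It would be wrong to infer that the planned models cannot give the week-12 difference. The defect is that the rule names other quantities and ranks neither. A second reply is that a condensed article leaves such detail to the analysis plan. That holds for covariance structure and similar choices, but here the article does state a rule.

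Several stronger readings are tempting but not supported:

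- **That the primary test is the interaction test, with 5% power.** Section 4.3 names no such test as primary. The 5% only shows what the interaction measures.
- **That a preliminary test selects the model.** The sentence puts one model after the other and states no selection rule.
- **That baseline is dropped from the second model.** The literal wording allows this, but the sentence before it sets baseline as a covariate. The natural reading is that only the interaction is removed.
- **That all six visits enter the primary model, or that baseline is an outcome row.** The first sits badly with the heading of Section 3.9, which separates week 12 from week 24. The second conflicts with "respective baseline values as covariates". Under the second, the week-12 interaction coefficient would in fact be the difference in change.

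Finally, the wording of Section 3.8 could mean an average over the 12 weeks, and Section 4.2 ties its 15 mm to no visit. The heading of Section 3.9 and the moderator paragraph favour week 12, but that is a reading of the text.

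**Conclusion.** The point holds in limited form. Section 4.3 gives two results as the treatment effect and makes neither primary. In general neither is the baseline-to-week-12 difference that the article indicates elsewhere and that matches its sample size.

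The size of the gap depends on how the benefit develops, which the article does not say. With a steady build-up to 15 mm at week 12, the main-effects estimate is 10 mm with 69–77% power, against 91% for the week-12 difference. With a constant benefit there is no bias and the averaged estimate has the higher power. These figures rest on the assumed correlation of 0.5 to 0.7, the common SD and the chosen profiles. That the named quantities differ in kind from the week-12 difference does not rest on them.

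**What to change.** Replace the sentence in Section 4.3 with, for example:

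*The primary estimate is the baseline-adjusted treatment difference in VAS pain at week 12, with its 95% CI, from the mixed model with treatment, categorical visit and treatment-by-visit. It is reported whatever the interaction result. The week-24 difference is secondary and the visit-averaged effect is supportive.*

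State also that the baseline value stays in every model. Covariance structure and a possible baseline-by-visit term are further choices that this point does not depend on.

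The cost is a change of wording before the data are analysed. The Data Availability statement describes the database as not yet analysed. No new data are needed, and the sample size stays as it is, because a week-12 difference with 49 per arm has the planned power. The one loss is precision if the benefit is in fact constant: the standard error is 4.55 mm instead of 3.71 to 4.07 mm under the assumptions above.
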